### Data monitoring

This study will not involve participants at risk of death or harmful interventions; therefore, there will be no need to create a data monitoring committee.

### Adverse effects

Adverse effects of PFMT are rare. Any discomfort or pain linked to treatment will be assessed. Volunteers will be closely monitored, asked about session discomfort, and adverse events documented. If risks arise, interventions halt. Withdrawn participants still factor into intention-to-treat analysis.

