**Methods:**

This study will be a randomized, controlled, parallel, and blinded clinical trial. The final sample will consist of 32 women diagnosed with SUI and cystocele (stage I and II). All volunteers will be assessed and reassessed using the same protocol: assessment form, gynecological examination, functional evaluation of PFM, and questionnaires to assess quality of life, urinary function, and sexual function. All volunteers will be evaluated for satisfaction levels post-treatment. The intervention will be PFMT, totaling 16 sessions to be conducted twice a week. Reevaluation will take place at the end of treatment and 1 month after completion of PFMT. Descriptive analysis and repeated measures ANOVA will be used for result analysis. A significance level of p<0.05 will be considered for all statistical tests.

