### Interventions

The intervention will involve individualized care, randomly divided into two groups: pelvic floor muscle training group (PFMTG) and comparator group (CG). The CG will receive informational content only, provided by a healthcare professional with expertise in urogynecology during a single visit. The educational material will encompass informative content about urinary incontinence, its risk factors, pelvic floor anatomy and function, types of UI, bladder and bowel functioning information, along with the significance of healthy lifestyle habits.

The PFMTG will receive similar educational material as the CG and will undergo 16 sessions conducted twice a week, totaling 2 months of treatment. The treatment for this group will encompass four exercise modalities: warm-up, breathing exercises, abdominal exercises, and pelvic mobility exercises. All exercises will involve pelvic floor muscle (PFM) activation. Progressions will be incorporated into each modality throughout the training.

In general, the breathing, abdominal, and pelvic mobility exercises will consist of two sets of eight repetitions during the first four weeks, progressing to three sets of eight repetitions in the final four weeks, except for the transversus contraction and plank exercises.

The PFMTG intervention will have an average duration of 45 minutes per session, with the initial five minutes dedicated to warm-up, 30 minutes for exercise execution, and approximately 10 minutes allocated to intervals between exercises.

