### Results

All assessments will be conducted by a blinded evaluator. The volunteers will undergo initial evaluation, including medical history, gynecological examination, functional assessment of the PFM, and questionnaires. The assessments will take place at three time points: before treatment (baseline assessment), at the end (final assessment), and one month after the last session (re-assessment). Fig 7 illustrates the assessment and re-assessment items.

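### The only adverse-event question named is tied to training sessions, which the comparator group does not have, so any description of harm by group would rest on unequal ascertainment

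*Protocol article*

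**What the plan says.** All references are to the protocol article.

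- **Adverse effects** sets out the procedure. First: "Any discomfort or pain linked to treatment will be assessed". Then: "Volunteers will be closely monitored, asked about session discomfort, and adverse events documented". The first sentence limits what is assessed to symptoms with a link to treatment. The second names one active question, about sessions, and adds documentation of adverse events with no such limit and no stated group, time point or window.
- **Interventions** gives the two groups very different contact. The PFMT group "will undergo 16 sessions conducted twice a week, totaling 2 months of treatment". For the comparator group: "The CG will receive informational content only, provided by a healthcare professional with expertise in urogynecology during a single visit".
- **Abstract, Methods** describes the assessments common to both groups: "All volunteers will be assessed and reassessed using the same protocol: assessment form, gynecological examination, functional evaluation of PFM, and questionnaires". The **Results** section places these at baseline, at the end of treatment and one month after the last session, all with a blinded evaluator. Neither place names an adverse-event item in the readable text. Fig 7, which shows the assessment and re-assessment items, is not available.
- The outcomes listed under **Results** include no harm outcome, and **Statistical analysis** describes no between-group comparison of harm.

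**The concern.** The article does not simply leave harm collection to another document. It states a procedure, and the two specific parts of that procedure, the link to treatment and the question about sessions, both depend on allocation. A woman in the comparator group has no session to be asked about, and one information visit is her only treatment contact. For the month after session 16, no question is stated for either group.

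The trial will probably report adverse events in some form, because the protocol says that they will be documented. A reader will then set the two groups' counts side by side, whether or not a test is planned. If one group was asked up to 16 times and the other only had what it volunteered, a difference could come from the asking alone. An excess in the PFMT group could be a product of collection. A low count in the comparator group could not serve as a background rate. The **Data monitoring** section dispenses with a committee on the ground that the intervention is not harmful, so the Adverse effects section is the main safety provision in the text.

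**Working it through.** The plan gives no figure on this point, so there is none to reproduce. The check counts opportunities to report and then shows what unequal detection does to the recorded counts.

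**Inputs from the article**
- PFMT group: 16 sessions (Interventions).
- Comparator group: 1 information visit, no sessions (Interventions).
- Both groups: 3 assessments, 2 of them after baseline (Results).
- Group size: 16 and 16 (Sample size).

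**Step 1: contacts**
- Scheduled contacts: PFMT 16 + 3 = 19; comparator 1 + 3 = 4.
- Contacts at which the session question can be asked: 16 against 0.
- Post-baseline contacts common to both groups: 2 against 2, with no adverse-event item named in the readable text.

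**Step 2: expected recorded events at equal true risk**

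Expected number of women with a recorded event = 16 × p × d. Here p is the true risk over the trial, the same in both groups, and d is the probability that an event is recorded. Both are assumptions; the article gives neither. With d = 1 for PFMT and d from 0 to 1 for the comparator group:

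| True risk p | PFMT, d = 1 | Comparator, d = 0 | d = 0.25 | d = 0.5 | d = 1 |
|---|---|---|---|---|---|
| 10% | 1.6 | 0 | 0.4 | 0.8 | 1.6 |
| 20% | 3.2 | 0 | 0.8 | 1.6 | 3.2 |
| 30% | 4.8 | 0 | 1.2 | 2.4 | 4.8 |

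The apparent difference is 16 × p × (d in PFMT − d in comparator). It vanishes only when detection is equal. The column d = 0 is the extreme, not the expected result: unfiltered documentation and two shared visits give comparator women some chance to report.

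Full detection with PFMT is also an upper case. If the link to treatment were applied strictly at sessions, background discomfort would be screened out there too, d in the PFMT group would fall, and the gap would shrink. So the size of the bias is unknown. What the text does show is that d is not made equal by design.

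**Step 3: what equal collection would and would not give**

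A common question at the two shared visits makes the opportunity 2 against 2. It does not make 16 per group informative. Two-sided Fisher power at 0.05, for assumed true rates:
- 30% against 10%: about 0.17
- 20% against 0%: about 0.20
- 40% against 10%: about 0.36

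Zero events in 16 women would still be compatible with a true rate up to 1 − 0.05^(1/16) = 17.1% (one-sided 95%) or 1 − 0.025^(1/16) = 20.6% (two-sided 95%). These limits come from the sample size and are the same before and after the fix.

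**The case against.** The strongest reply is that the article breaks no promise. Its aims, outcomes and analysis include no between-group harm comparison. The documentation of adverse events carries no filter, and its subject is volunteers, a word used elsewhere for both groups. The assessment items are in a figure that cannot be seen, the content of the assessment form is not described, and a journal article commonly leaves adverse-event forms to the full protocol. All of this stands, and it limits the point.

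It also rules out several stronger readings that a reader might infer:

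- *That the trial cannot compare harm.* Both groups attend two post-baseline assessments where a common question could be asked, and may already be.
- *That comparator events are close to zero by construction.* Unfiltered documentation may cover that group, so zero is only one end of the range.
- *That relatedness is judged at sessions by staff who know the allocation, or that collection stops at session 16.* The article does not say who judges relatedness or when, and gives no end point for documentation.
- *That the Introduction's remark on few complications obliges the trial to make a safety comparison.* That remark is background setting PFMT against surgery, and this trial has no surgical group.

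What the reply does not remove is the asymmetry. The one question that is named can reach only one group, and documentation without a question leaves the other to spontaneous report.

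**Conclusion.** The point holds in a limited form. As stated, active questioning about harm is tied to sessions, and the assessment of pain or discomfort is tied to a link with treatment. Only the PFMT group has sessions, and the readable text states no adverse-event question for the comparator group or for the month after training. Any description of harm by group would therefore be biased by unequal ascertainment.

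The size cannot be fixed from the article. Under an assumed equal risk of 20% and full detection with PFMT, the apparent excess lies between 0 and 3.2 women of 16, depending on comparator detection.

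The conclusion assumes that the figure not shown and the full protocol do not already contain a common question; if they do, one sentence in the Adverse effects section settles the matter. No planned analysis is invalidated, and harms would be descriptive at this sample size in any case. The gain is symmetric collection, not power.

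**What to change.** In the Adverse effects section:

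1. State that all adverse events are recorded whatever their presumed cause, with relatedness recorded as a separate item.
2. Have women in both groups complete the same short written adverse-event question at the final assessment and at the one-month re-assessment, covering the time since the previous assessment. Collect it so that the answers do not reveal allocation to the blinded evaluator, for example on a form returned to someone else.
3. Describe harm by group from these two common time points only. Report events noted at sessions separately, labelled as data from the PFMT group alone.

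No extra visit and no change to treatment is needed. The cost is a few minutes at each of two existing visits and one more table. The reported event count may also be higher than under the present wording.
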